### Sample size determination

3.8.

Based on literature [51] and our pilot studies [26,33,52–54], we assume an intraclass correlation coefficient (ICC) of 0.03 among daycare centers and an ICC of 0.02 among classrooms. Because some daycare center variation will be accounted for when classroom is also included as a random effect and vice versa, we expect the combined ICC to be 0.04, slightly smaller than the sum of 0.03 and 0.02. We expect to achieve a small-to-medium effect size of 0.35 for the selected primary outcome of preschoolers’ problem behaviors rated by teachers from baseline to immediately post-intervention, with a significance level of 0.05, sample size of 50 daycare centers (on average 8 dyads/center, range 5–14, 400 dyads) can achieve at least 86 % power.

### Data analysis

3.9.

All data analyses will be performed using IBM SPSS Statistics 27, SAS 9.4, or Mplus version 8.8. A *p*-value ≤0.05 will indicate statistical significance. All analyses will use intention-to-treat principle. The unit of randomization is ‘daycare center,’ so unit of analysis will be participants nested within each daycare center and each classroom. Comparisons of baseline demographic characteristics between groups will be made using two-sample *t*-tests for continuous variables and Chi-square tests (or Fisher’s exact tests) for discrete variables. If group differences are observed, relevant variables will be treated as covariates in post-intervention and follow-up analyses. To evaluate potential attrition bias, participants who drop out will be compared to those who remain in the study on demographics as well as baseline outcomes. Any characteristics or outcomes related to attrition will be included as covariates in analyses.

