#### Missing data

3.9.1.

Statistical models will incorporate missing at random mechanisms [55] and derived inferences using full information maximum likelihood methods. For methods that require complete data, we will impute missing values using multiple imputations (*n* = 20) with PROC MI in SAS and IVEware SAS macro. Summary analyses from the 20 imputations will then be performed using SAS PROC MIANALYZE. To further examine the effects of missing data on results, we will perform sensitivity analysis to examine if the analysis results vary between non-imputed data and imputed data.

#### Aim 1 & 2

3.9.2.

Separate linear mixed-effect models will be used to determine the intervention effects on each outcome. Each model will include an interaction between group (intervention vs. control) and time (Month 4 and Month 16), baseline outcome, subject level random effects to account for repeated measures on the same subject over time, and cluster-specific random effects. Potential confounders that are identified in the baseline group comparisons and the cohort attrition analysis will be included in the model. We will also examine potential moderators (e.g., sex, ethnicity/race) of the intervention effects. In case there is a significant interaction, we will conduct post-hoc analyses to examine how the intervention effects differ at different levels of baseline outcome. Effect size Cohen’s *d* and 95 % confidence interval will be calculated.

#### Aim 3

3.9.3.

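### Covariates beyond the baseline outcome are selected by unclustered baseline significance tests, so adjustment follows chance imbalance, not prognosis, at a cost in precision but not in false positives

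*Protocol article*

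**What the plan says.** Three statements in section 3.9 (Data analysis) work together. The general threshold is "A *p*-value ≤0.05 will indicate statistical significance". The baseline comparison is "Comparisons of baseline demographic characteristics between groups will be made using two-sample *t*-tests for continuous variables and Chi-square tests (or Fisher’s exact tests) for discrete" measures. The consequence is "If group differences are observed, relevant variables will be treated as covariates in post-intervention and follow-up analyses". A second rule covers dropout: "Any characteristics or outcomes related to attrition will be included as covariates in analyses".

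Section 3.9.2 (Aim 1 & 2) repeats both rules for the outcome models, which include the primary outcome: "Potential confounders that are identified in the baseline group comparisons and the cohort attrition analysis will be included in the model". The terms fixed in advance are given just before: "Each model will include an interaction between group (intervention vs. control) and time (Month 4 and Month 16), baseline outcome, subject level random effects", plus cluster random effects.

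Two other statements bear on this. Section 3.9 recognizes the clustering: "The unit of randomization is ‘daycare center,’ so unit of analysis will be participants nested within each daycare center and each classroom". Section 3.3 (Randomization) allocates centers straight after baseline data collection. It constrains the allocation on urban/rural setting, center size and ethnicity/race, but section 3.9.2 does not list these three factors as model terms.

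**The concern.** Because allocation comes after baseline measurement, a baseline difference between arms can only be a chance result of the allocation. A significance test of that difference answers no useful question, and calling the flagged variables potential confounders misdescribes them.

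The rule also selects on the wrong property. Adjustment in a randomized trial gains precision to the extent that a covariate predicts the outcome. Selection by imbalance can bring in a variable unrelated to problem behaviors and leave out a strong predictor that happens to be balanced. The constrained factors are the clearest case: the design makes them balanced, so a screen for imbalance will rarely admit them, and center-level factors may not count as demographic characteristics at all.

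The named tests also treat about 400 children as independent although 50 centers are randomized, so they flag differences more often than 5% of the time. Finally, the words observed and relevant leave someone to decide, after seeing data, which covariates go in.

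This is not a detail left to an analysis plan. The article states the rule in two places, and an analysis plan that follows the article would inherit it.

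**Working it through.** **Inputs.** Section 3.8: 50 centers, mean 8 dyads (range 5–14), 400 dyads, combined ICC 0.04, effect size 0.35. Section 3.9: threshold 0.05, taken as two-sided. Table 2: 12 socio-demographic items. ICCs for demographic variables are not given, so a range is assumed.

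**The plan's own figure first.** Design effect = 1 + (8 − 1) × 0.04 = 1.28. Effective n per arm = 200 / 1.28 = 156.25. Noncentrality = 0.35 / √(2/156.25) = 3.09. Power is 87.2% by normal approximation and 85.8% by noncentral t on 48 df, against the stated 86%. The figure reproduces, and this point does not change it.

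**True size of the unclustered baseline test.** Size = 2 × [1 − Φ(1.96/√DEFF)], with DEFF = 1 + 7 × ICC.

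| ICC of the baseline variable | DEFF | True size |
|---|---|---|
| 0.01 (assumed) | 1.07 | 5.8% |
| 0.04 (plan's outcome ICC) | 1.28 | 8.3% |
| 0.10 (assumed) | 1.70 | 13.3% |
| 0.20 (assumed) | 2.40 | 20.6% |

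A simulation with center sizes of 5 to 14 gives 8.9%, 13.9% and 21.8% for the last three rows.

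**Covariates flagged by chance.** With k independent candidates, the expected number is k × size and the chance of at least one is 1 − (1 − size)^k.

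- k = 12, size 8.3%: 1.0 expected; chance of at least one 65%.
- k = 12, size 20.6%: 2.5 expected.
- k = 12, size 5% (a correct test): 0.6 expected; chance of at least one 46%.
- k = 6: 41% at size 8.3%, 26% at size 5%.

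The 46% shows that replacing the tests with clustered ones would not cure the rule.

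**What happens to the treatment test.** The figures above describe the screening test only. Two simulations of the whole procedure were made under no treatment effect: 50 centers of 8, 12 candidates, 6,000 runs per scenario, prognostic strengths assumed. Attrition selection was not modeled.

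- Random-effects outcome model without the baseline outcome, outcome ICC 0.04, candidates jointly correlated with the outcome. Type I error was 4.8% with non-prognostic candidates (candidate ICC 0.04). At joint correlations 0.3 and 0.6 it was 4.6% and 3.4% (candidate ICC 0.04), and 5.1% and 2.3% (candidate ICC 0.20). Unadjusted or fully adjusted models gave 4.5–5.9%.
- Cluster-robust test, one prognostic candidate. At candidate ICC 0.20 and correlation 0.5, the rule gave 3.4%, against 5.3% with that variable prespecified. At correlation 0.3 it gave 4.5–4.6%.

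The Monte Carlo standard error at 5% is √(0.05 × 0.95/6000) = 0.28 percentage points, so 5.1% is indistinguishable from nominal. The direction has a simple reason. When a prognostic variable is imbalanced, the rule adjusts for it. When it is balanced, the rule leaves it in the residual and reports a standard error larger than that balanced allocation warrants.

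**Precision at stake.** If covariates left out have joint correlation r with the outcome, given what is already in the model, including them cuts the residual variance by r²: 9% at r = 0.3 and 36% at r = 0.6. Both r values are assumed. Because the baseline outcome is already included, the lower end is more plausible.

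**The case against.** The strongest defense is that the screen never looks at the outcome, the procedure is itself stated in advance, and the baseline outcome, probably the most prognostic variable, is in every model. One to 2.5 noise covariates among about 400 children cost almost nothing. All of this stands, and it limits the point.

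It also rules out some stronger readings that a reader might infer:

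- *That the 8.3% or 65% is an error rate of the trial's conclusion.* It is not. It belongs to the baseline screen, and the simulations show type I error for the treatment effect at or below nominal.
- *That the primary model is unknown until data are seen.* This is too broad. Section 3.9.2 fixes the group-by-time term, the baseline outcome and the random effects; only the further covariates vary.
- *That 65% is a firm figure.* It assumes 12 independent items that share the plan's outcome ICC. Income, education, employment and marital status are plausibly correlated, and race is constrained by design, so it would be flagged less often.
- *That predictors of dropout should move out of the model into imputation.* Section 3.9.1 uses full-information maximum likelihood under missing at random and imputes only for methods that need complete data. For the likelihood-based mixed model such a move would do nothing, whereas baseline predictors of dropout kept as covariates can make missing at random more plausible.

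The defense does not answer why covariates should be chosen by imbalance, or why the factors used to constrain the allocation are absent from the listed model terms.

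**Conclusion.** The point holds in a limited form. Beyond the baseline outcome, the adjustment set is chosen by tests that have no valid purpose after randomization and that are also mis-sized for clustered data: about 8.3% for a nominal 5% test if demographics share the plan's ICC of 0.04, and 13–21% at assumed ICCs of 0.10–0.20. The consequences are lost precision, inference that ranges from nominal to somewhat conservative (simulated type I error of 2.3–5.1%, depending on assumed prognostic strength), and an avoidable choice after data are seen. The material does not support a claim of false-positive inflation or of bias in the estimate. The loss is small if demographics add little to the baseline outcome and larger if they predict strongly. The change should be made because it is better and nearly free; the trial's validity does not depend on it.

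**What to change.** In section 3.9, delete the rule that turns baseline group differences into covariates, and report baseline characteristics by arm descriptively, without tests. In section 3.9.2, replace the sentence on identified confounders with one covariate set, fixed in advance for all Aim 1 and 2 models:

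- the baseline value of the outcome;
- the constrained-randomization factors: urban/rural setting, center size and ethnicity/race;
- a short list of prognostic baseline variables chosen before outcome data are seen, for example child age and sex (the exact list is for the investigators to choose).

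Baseline predictors of dropout may stay in the likelihood-based model to support missing at random. Name them in advance where possible, and show results with and without any added after follow-up.

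The cost is a few degrees of freedom and a change of wording. All the variables are already collected, and the sample size does not change.

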#### Missing data

3.9.1.

Statistical models will incorporate missing at random mechanisms [55] and derived inferences using full information maximum likelihood methods. For methods that require complete data, we will impute missing values using multiple imputations (*n* = 20) with PROC MI in SAS and IVEware SAS macro. Summary analyses from the 20 imputations will then be performed using SAS PROC MIANALYZE. To further examine the effects of missing data on results, we will perform sensitivity analysis to examine if the analysis results vary between non-imputed data and imputed data.

#### Aim 1 & 2

3.9.2.

Separate linear mixed-effect models will be used to determine the intervention effects on each outcome. Each model will include an interaction between group (intervention vs. control) and time (Month 4 and Month 16), baseline outcome, subject level random effects to account for repeated measures on the same subject over time, and cluster-specific random effects. Potential confounders that are identified in the baseline group comparisons and the cohort attrition analysis will be included in the model. We will also examine potential moderators (e.g., sex, ethnicity/race) of the intervention effects. In case there is a significant interaction, we will conduct post-hoc analyses to examine how the intervention effects differ at different levels of baseline outcome. Effect size Cohen’s *d* and 95 % confidence interval will be calculated.

#### Aim 3

3.9.3.

For the outcome constructs with multiple survey items, we will create composite scores (latent variables) based on results from confirmatory factor analysis. We will apply the 5-step structural equation modeling procedure: model specification, model identification, parameter estimation, model evaluation, and model modification. Hypothesized relationships (model specification) are driven by theoretical models. Model identification will be determined to make sure the model can be identified. A covariance matrix will be used for analysis, and parameter estimation will apply full information maximum likelihood approach. Both standardized and unstandardized coefficients will be calculated. Model fit will be evaluated via Tucker-Lewis Index (TLI ≥0.90), Comparative Fit Index (CFI ≥0.90), standardized root mean squared residual (SRMR ≤0.08), and root mean squared error of approximation (RMSEA ≤0.06) [56]. If model does not fit the data well, model modification will be conducted. Theoretical framework and literature results will be considered when modifying the model.

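### The only missing-data sensitivity analysis sets one missing-at-random analysis against another, so for the Aim 1 and 2 models agreement cannot show robustness to outcome-dependent dropout

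*Protocol article*

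**What the plan says.** Section 3.9.1 of the protocol article sets the assumption: "Statistical models will incorporate missing at random mechanisms", with inference by full information maximum likelihood. Imputation has a limited role: "For methods that require complete data, we will impute missing values using multiple imputations", with 20 imputations, run "with PROC MI in SAS and IVEware SAS macro". The section then adds one check on the influence of missing data, a "sensitivity analysis to examine if the analysis results vary between non-imputed data and imputed data". It names no analysis that departs from MAR.

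Section 3.9.2 fits the Aim 1 and 2 outcomes with linear mixed models that carry "subject level random effects to account for repeated measures on the same subject over time, and cluster-specific random effects". Section 3.9 compares dropouts with completers on demographics and baseline outcomes, and adds whatever is related to attrition as covariates.

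The primary outcome is teacher-rated problem behaviors on the PKBS-2 (section 3.6). Section 3.8 powers it for the change from baseline to immediately post-intervention.

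**The concern.** A sensitivity analysis is informative when it changes the assumption in doubt. Here that assumption is MAR: given what was observed, whether a score is missing does not depend on the score itself. The non-imputed mixed model relies on it. So does standard multiple imputation, and no shift or pattern-mixture step is described. Changing the computing method while keeping the assumption gives two estimates of the same quantity.

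The risk lies in how the result would be read. Close agreement is the expected outcome, and it would naturally be reported as robustness to missing data. The Discussion (section 4) foresees difficulty retaining families and incomplete measures, and offers multiple imputation as a way to limit the resulting bias. If children whose behavior worsens are more often lost from the intervention arm, both analyses overstate the benefit by about the same amount.

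**Working it through.** **1. The plan's own figure.** Inputs from sections 3.1 and 3.8: 25 centers per arm, mean 8 dyads per center, combined ICC 0.04, effect 0.35 SD, alpha 0.05 (taken as two-sided).
- Design effect: 1 + (8 - 1) x 0.04 = 1.28.
- Effective number per arm: 200 / 1.28 = 156.25.
- SE of the difference: sqrt(2 / 156.25) = 0.113 SD.
- Power: Phi(0.35 / 0.113 - 1.96) = 87.2%, or 85.8% using t with 48 df. The stated power of at least 86% is reproduced to within rounding and method.

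**2. What each side of the comparison assumes (Aims 1 and 2).**

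| Side | Method | Assumption |
|---|---|---|
| Non-imputed | Mixed model by likelihood on observed data | MAR |
| Imputed | Standard multiple imputation, then the same model | MAR |

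If the imputation used extra predictors, the two could differ somewhat. That difference would reflect the predictors and would not test MAR.

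**3. Simulation of the comparison.** The settings are assumptions except where the plan gives them: 50 clusters of 8, ICC 0.04, baseline-outcome correlation 0.5, one post-baseline visit, 20 imputations, 1,500 runs per setting and a true effect of 0. In the intervention arm, higher (worse) outcomes were more likely to be missing. Negative estimates favor the intervention.

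| Nominal missing | Likelihood estimate (SD) | Imputed estimate (SD) | False rejection: likelihood / imputed |
|---|---|---|---|
| 10% | -0.088 | -0.089 | 12.5% / 13.5% |
| 20% | -0.151 | -0.152 | 29.3% / 31.0% |
| 30% | -0.211 | -0.212 | 45.9% / 48.5% |

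The two estimates never differ by more than 0.001 SD, while both are biased by 0.09 to 0.21 SD.

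**4. What a delta adjustment would show.** Let p be the fraction of intervention-arm scores missing, and delta the amount by which those children are worse than MAR predicts. The adjusted effect is 0.35 - p x delta.

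| p | delta 0.2 | delta 0.35 | delta 0.5 |
|---|---|---|---|
| 10% | 0.33 | 0.315 | 0.30 |
| 20% | 0.31 | 0.28 | 0.25 |
| 30% | 0.29 | 0.245 | 0.20 |

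The plan gives no dropout rate for this trial, so p and delta are assumed ranges.

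**5. Rough tipping point if 0.35 SD is observed.** This uses the step 1 formulas with 8 x (1 - p) children per center and 1.96 as the critical value.
- 20% missing: 6.4 per center, design effect 1 + 5.4 x 0.04 = 1.216, effective n 160 / 1.216 = 131.6, SE 0.123, smallest significant effect 1.96 x 0.1233 = 0.242. Tipping shift: (0.35 - 0.242) / 0.20 = 0.54 SD.
- 30% missing: 5.6 per center, design effect 1.184, effective n 140 / 1.184 = 118.2, SE 0.130, smallest significant effect 0.255. Tipping shift: 0.095 / 0.30 = 0.32 SD.

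These values ignore the gain from baseline adjustment and any change in variance caused by the shift. They show that the tipping value depends strongly on how much is missing, which the planned comparison cannot reveal.

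**The case against.** **The attrition covariates.** Section 3.9 already examines dropout against baseline outcomes, which include problem behaviors and caregiver stress, and adjusts for what it finds. This stands as far as it goes: dropout explained by those measured baseline values is covered. Dropout that depends on an unobserved Month 4 score is not, and covariates make MAR more plausible without testing it.

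**Complete-case comparisons.** For a method that needs complete data, non-imputed means complete cases, which rest on a different and usually stricter assumption than MAR. The comparison is then not empty, so it would be too strong to call it worthless in general. It is still not an analysis under departure from MAR, and the Aim 1 and 2 models are not such methods.

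**Dropout may be small.** The feasibility study had 0% attrition (section 1). It was a 5-week, single-group study of 19 preschoolers, whereas this trial measures at Months 4 and 16. The objection still means that no size can be attached without an assumed dropout rate.

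**A detail for the analysis plan.** A condensed article may leave sensitivity analyses to a fuller document. Here, however, the article states the check and its purpose, and the stated check does not serve that purpose for the main models.

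**A stronger reading.** A reader might infer that the imputation and the Aim 3 structural equation model are single-level, so that standard errors are too small. The documents do not support this:
- Neither step is called single-level. Section 3.9 says for the analyses generally that the "unit of analysis will be participants nested within each daycare center and each classroom", and lists software that can handle clustering: "All data analyses will be performed using IBM SPSS Statistics 27, SAS 9.4, or Mplus version 8.8".
- Aims 1 and 2 use likelihood with cluster random effects, and section 3.9.3 also uses likelihood: "A covariance matrix will be used for analysis, and parameter estimation will apply full information maximum likelihood approach". Neither needs imputed data.
- A shortcut, ICC x (1 - p)^2, suggests that single-level imputation would shrink SEs by 4% to 6%. Simulation of single-level imputation followed by a cluster-aware model under MAR does not bear this out: model SE over empirical SE was 0.991 to 0.996, with type I error of 4.5% to 4.7%.
- Only if the structural equation model ignored center would there be a material effect. For a center-level contrast at ICC 0.04, the SE ratio would be 1 / sqrt(1.28) = 0.884, an 11.6% understatement, with 8.3% type I error. The article does not say that center is ignored.

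**Conclusion.** The concern holds in a limited form. For the Aim 1 and 2 mixed models, including the primary outcome, the planned comparison cannot detect or bound bias from dropout that depends on unobserved post-baseline scores, and agreement should not be reported as evidence against such bias. The logic needs no dropout figure, because it follows from the shared assumption. The size does need one: in the assumed scenarios the shared bias was 0.09 to 0.21 SD under no true effect, and a planned 0.35 SD effect fell to between 0.20 and 0.33 SD.

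This does not show that MAR fails in this trial or that the primary analysis is wrong. A likelihood mixed model under MAR is a reasonable main analysis. Cluster handling in the Aim 3 model is at most a point to clarify.

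**What to change.** Keep the imputed versus non-imputed comparison if wanted, but do not present it as a check on MAR. Add a delta-adjusted (tipping-point) multiple imputation of teacher-rated PKBS-2 problem behaviors at Month 4:
- impute under MAR with the baseline score, the attrition predictors and center in the imputation model;
- shift the imputed intervention-arm scores toward worse in steps, for example 0.1 SD;
- refit the primary model at each step, and report the estimates and the shift at which significance is lost.

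One sentence in section 3.9.3 saying how the structural equation model accounts for center and classroom would settle the clarification point.

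The cost is some extra programming in software the plan already names and one more reported analysis. The primary model, sample size and data collection do not change.

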### Design and setting

3.1.

The cluster randomized controlled trial (ClinicalTrials.gov ID: NCT06597474) will be conducted in 50 Michigan Head Start daycare centers from 2024 to 2028, with participant enrollment from 2024 to 2027. Fifty Head Start daycare centers will be randomized into the intervention (*n* = 25: 8 urban and 17 rural daycare centers) or usual care control group (n = 25: 8 urban and 17 rural daycare centers). On average, eight caregiver-preschooler dyads will be recruited from each daycare center (total 400 dyads). All outcomes will be assessed at baseline (Month 0), post-intervention (Month 4), and 12-month follow-up (Month 16). Fig. 1 demonstrates the study flow diagram.

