### Randomization

3.3.

We will apply a covariate-constrained randomization schema to ensure that the intervention and control groups are balanced with respect to urban/rural setting, daycare sizes, and preschoolers’ ethnicity/race distributions at baseline. Immediately after baseline data collection, the study blinded statistician will generate 100,000 possible simple random allocation schemes. For each allocation scheme, balance will be estimated on the selected baseline characteristics according to the absolute difference. A constrained randomization space containing 10 % of the best allocations will be chosen, and one allocation scheme will be randomly selected from this constrained randomization space to determine the composition of the two groups.

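### The three factors that constrain the randomisation are not in the outcome model, and the covariate rule tends to keep them out; the cost is a slightly conservative test and a little forgone power

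*Protocol article*

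**What the plan says.** Section 3.3 (Randomization) of the protocol article describes covariate-constrained randomisation. The statistician generates 100,000 allocations, scores each on absolute differences, keeps the best 10% and draws one. The aim is arms that are "balanced with respect to urban/rural setting, daycare sizes, and" the children's ethnicity/race distribution. Section 3.1 (Design and setting) fixes the result for setting: each arm has "8 urban and 17 rural daycare centers".

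Section 3.9.2 (Aim 1 & 2) lists the model terms: group by time, baseline outcome, subject random effects and cluster random effects. None of the three constraining factors is listed. Two sentences govern further covariates. In 3.9: "If group differences are observed, relevant variables will be treated as covariates in post-intervention and follow-up analyses". In 3.9.2: "Potential confounders that are identified in the baseline group comparisons and the cohort attrition analysis will be included in the model". Section 3.9 also carries variables related to attrition into the models. Ethnicity/race appears otherwise only as an example of a possible moderator.

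**The concern.** The design and the covariate rule pull in opposite directions. The randomisation removes arm differences on the three factors, and the analysis then admits a factor mainly because the arms differ on it. Setting is the clearest case. With the same urban/rural split in each arm, a centre-level comparison can show no difference. Setting and centre size are also not among the examples of demographics in Table 2, so they may never be tested at all. Race is among them, but it would enter only by chance imbalance or through attrition.

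Constraining on a prognostic factor reduces the true sampling variance of the treatment effect. A model without that factor cannot see the reduction and reports a standard error that is too large. The test then runs below its nominal level, the intervals are too wide, and part of the precision gained by the design is not used.

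**Working it through.** **Inputs from section 3.8:** "small-to-medium effect size of 0.35"; "with a significance level of 0.05" (two-sided assumed); "we expect the combined ICC to be 0.04"; and "sample size of 50 daycare centers (on average 8 dyads/center, range 5–14, 400 dyads) can achieve at least 86 % power". From 3.1: 25 centres per arm. From 3.3: the best 10% of allocations. The documents do not say how much between-centre variance the factors explain, so the share f is an assumption, varied from 0 to 100%.

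**Step 1: the plan's own power.** Design effect = 1 + (8 − 1) × 0.04 = 1.28. Effective n per arm = 200 / 1.28 = 156.25. Standardised difference = 0.35 × √(156.25 / 2) = 3.094. Power = Φ(3.094 − 1.96) = 87.2%, or 85.8% with a noncentral t on 48 df. With a coefficient of variation of centre size of 0.30 (assumed), the design effect is 1 + (1.09 × 8 − 1) × 0.04 = 1.309, and power is 86.4% (normal) or 85.0% (t). The stated 86% is reproduced.

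**Step 2: closed-form check, no baseline term.** With total variance 1, a centre mean of 8 children has variance 0.04 + 0.96 / 8 = 0.16. If the constraint balanced the factors perfectly, the true variance would be 0.16 − 0.04f, while the model without the factors still uses about 0.16. The ratio of true to reported standard error is √[(0.16 − 0.04f) / 0.16], and the actual type I error is 2 × [1 − Φ(1.96 / ratio)].

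- f = 25%: ratio 0.968, type I error 4.3%
- f = 50%: ratio 0.935, type I error 3.6%
- f = 75%: ratio 0.901, type I error 3.0%
- f = 100%: ratio 0.866, type I error 2.4%

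**Step 3: simulation, no baseline term.** There were 50 centres (16 urban, 34 rural, sizes 5 to 14, one race-share variable), with an allocation drawn from the best 10% of 400 per trial. A REML random-intercept model was fitted with and without the three factors, with 12,000 trials per cell at ICC 0.04.

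| f | Type I, omitted | Type I, included | Power, omitted | Power, included |
|---|---|---|---|---|
| 0% | 5.0% | 5.0% | 85.02% | 84.35% |
| 25% | 4.2% | 4.7% | 85.56% | 86.59% |
| 50% | 3.7% | 4.3% | 85.88% | 88.44% |
| 75% | 3.0% | 4.1% | 86.57% | 90.25% |
| 100% | 2.5% | 4.0% | 87.32% | 92.14% |

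Power forgone by omission is 1.0, 2.6, 3.7 and 4.8 points for f = 25 to 100%. The included column falls below 5% partly because the variance component is bounded at zero when the ICC is small. As a control, simple randomisation with f = 50% gives 4.8% for the model without the factors, so the shortfall comes from the constraint combined with the omission.

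**Step 4: with the baseline outcome in the model, as 3.9.2 specifies.** ICC 0.04, f = 50%, two separate simulations.

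- Centre-level test, 4,000 trials per cell, factor effects equal at baseline and follow-up. Without the baseline term: 3.7% omitted against 5.0% included. With it, by baseline/follow-up correlation r: 3.8% against 4.1% (r = 0.4), 4.6% against 4.8% (r = 0.6), 4.9% against 5.2% (r = 0.7). Power differs by at most 0.4 points (93.6% against 94.0% at r = 0.4), though it is near its ceiling. Monte Carlo error on type I is about 0.3 points.
- Independent repeat. Without the baseline term: 4.0% against 4.9%. With it, for r of 0.4 to 0.6: 4.2–4.8% against 4.9–5.1%. If the factors affect follow-up but not baseline: about 2.8% against 4.6%.

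The r values are assumptions; Table 2 gives PKBS-2 test-retest reliability of 0.58 to 0.87.

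**The case against.** The strongest objection is that every model contains the baseline outcome. A centre factor that shifts behaviour scores will usually shift them at baseline too, so baseline adjustment removes much of its effect. Step 4 bears this out, and this part of the objection stands: a calculation without the baseline term overstates the problem. It does not remove the point, because a factor that acts on change and not on level is not absorbed.

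It can also be said that a condensed article leaves exact covariates to the analysis plan, and that the list in 3.9.2 is not called exhaustive. That would answer a complaint about missing detail. Here, however, the article states how covariates are chosen, and that rule works against the design.

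A reader might infer more: that the trial is underpowered, that its primary test is unsound, or that power is lost however little the factors matter. The documents support none of these. Without the factors the model still has about 85 to 87% power before any gain from baseline adjustment, in line with the stated figure. The error is conservative, so false positives are not inflated and the estimate is not biased. At f = 0 nothing is lost, and no section says that these factors predict problem behaviours. Much larger losses can be produced with an ICC of 0.10 or 0.20, but section 3.8 plans for 0.04 and the article gives no such values.

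**Conclusion.** The point holds as a badly fixed covariate rule of minor to moderate importance. The analysis does not carry the factors that the randomisation was constrained on, and the stated selection rule will tend to leave them out.

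The consequence is confined to efficiency. At ICC 0.04 with half the centre variance explained, the test runs at about 4% without baseline adjustment. The gap is 0 to 1 point with the baseline outcome in the model, and the test runs at about 3% if the factors act on change only. These sizes rest on the assumed explained share, the assumed baseline correlation, and a single race-share variable standing in for the ethnicity/race distribution.

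**What to change.** In 3.9.2, prespecify urban/rural setting, centre size and centre ethnicity/race composition, coded as in the constraint, as fixed effects in every Aim 1 and Aim 2 model, whatever the baseline comparisons show. A randomisation test over the constrained set of allocations would be an alternative way to respect the design.

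The cost is one sentence and about 3 of 48 centre-level degrees of freedom, or a few more if ethnicity/race composition is coded in several categories. No new data are needed. If the factors turn out not to be prognostic, the price is about two thirds of a point of power (85.02% against 84.35% in step 3). The change should be made before outcomes are analysed.
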